**Fig. 1 Fig1:**
[figure not shown]
The consort flow diagram

## Methods: participants, interventions, and outcomes

### Study setting {9}

Participants will be recruited between June 2022 and August 2022 in Iran. Ethical approval for the study was obtained from the Research Ethics Committees of Lorestan University of Medical Sciences (reference number: IR.LUMS.REC.1399.269). The trial has been registered at (ISRCTN36198096). The study was found to be in accordance with the national norms per the Helsinki Declaration.

### Eligibility criteria {10}

The nurses who are included in the care of COVID-19 patients will be recruited in this study.

The inclusion criteria are:Age ≥ 18 yearsInsomnia Index Scale ≥ 15Willing to participateAccess to the Internet and have an email addressMeeting the *Structured Clinical Interview for DSM-IV Axis I Disorders* criteria for insomnia [72, 73].

*Exclusion criteria:*
Receiving psychological interventions during this studyPregnancy or breastfeedingMissed three consecutive sessions

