### Intervention description {11a}

#### Interventions

The study (e.g., all assessments and treatments) will be administered online. All participants s will be requested not to change their lifestyle during the study and continue their daily routines, exercise, diet, and medications, and, if received any psychological treatment, inform the researchers. Each participants who receive positive COVID-19 test will be exempted to continue the trial. Before each session, participants will be requested to feel free in case of unpleasant experiences, potentially related to the trial. In case of emergency, the participant will receive further evaluation to make decision about continue or discontinue.

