### Sample size {14}

The sample size is calculated according to the minimal difference recommendation for non-inferiority design [85]. The minimal important difference in the severity of insomnia is a decrease of eight scores on the ISI [84]. The non-inferiority margin is half the difference (4 points on ISI). Therefore, the treatment groups will be considered equivalent if their average ISI total scores do not differ by more than 4 points. Therefore, the study will detect the minimum clinically significant difference at a one-tailed test, 5% significance level, and 80% power. Finally, 64 participants will be required. Anticipation of 25% dropout rate, the required sample size was 80. To reach the desired sample size, the link for the study will be distributed and posted on online medical staff forums. Also, the trial information will be emailed to psychologist and psychiatrist to share the trial with their clients.

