### Data management {19}

The data will be collected via the Internet. The participants will complete the primary and secondary outcomes at three-time points: time 1: pretreatment to allocation, including baseline (week 1); time 2: immediately after the intervention, including post-treatment assessment (week 10), and time 3: 1-month follow-up (week 14). The data will be automatically coded and depersonalized and stored on a secure server. Before recruitment, the study protocol was designed with a concentrate on ensuring data quality through standardization of data collection processes. Data collection instruments were designed with validated items. Also, instrument guides were utilized as a reference for data collectors and supervisor, which included instructions for how to use instruments, definitions, and interpretation guidelines for each question. Also, all research team members received a comprehensive refresh course in the context of psychological assessments and ethics in clinical research. The supervisor ensure that each operation will be performed to a standard.

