## Statistical methods

### Statistical methods for primary and secondary outcomes {20a}

Main analyses will be conducted on the intent-to-treat (ITT) approach, including all randomly allocated participants, regardless of attendance. The last observation carried forward (LOCF) method is one way to handle missing data. In LOCF approach, the missing data are replaced by the last observed value of that variable. The time points for the observations of missed values will be reported. Descriptive statistics will be utilized to present the continuous variables as the means and SDs and categorical variables as the numbers and percentages.

To determine whether the IMBSR is inferior to ICBT-I, the confidence interval approach was used. Non-inferiority analysis will be assessed using an *F* test statistic generated from the linear mixed model and confidence intervals [86]. This tests whether the difference between the group means is statistically larger than the non-inferiority margin (clinically significant difference) and if the upper limit of the one-sided confidence interval of the difference between the group means is less than the pre-specified margin of non-inferiority. A non-inferiority margin of 4 points on ISI is chosen for the analysis. This means that the mean difference between the groups should not be more than 4 points in favor of ICBT-I, to establish noninferiority of IMBSR. Repeated-measures analyses of variance (ANOVAs) two (condition: iMBSR *vs*. iCBT-I) × three (time point: time1, time2, time3) will be designed to compare the main treatment effects of the conditions on secondary outcomes. The values of effect sizes are presented as partial eta squared and Cohen’s *d.*

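### An attendance-based exclusion that can only occur after randomisation conflicts with the all-randomised analysis, and the protocol does not say whether the ISI is still collected after such an exit

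*Protocol article*

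**What the plan says.** Four parts of the protocol article bear on who stays in the trial.

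- **Eligibility criteria {10}** gives the exclusions as "Receiving psychological interventions during this studyPregnancy or breastfeedingMissed three consecutive sessions" (three list items run together).
- **Interventions, under {11a}**, adds: "Each participants who receive positive COVID-19 test will be exempted to continue the trial". For other psychological treatment the same paragraph only asks participants, "if received any psychological treatment, inform the researchers".
- **Relevant concomitant care {11d}** rules out other experimental treatment and refers back to the exclusion criteria.
- **Statistical methods {20a}** states: "Main analyses will be conducted on the intent-to-treat (ITT) approach, including all randomly allocated participants, regardless of attendance". The only missing-data method it names is LOCF: "In LOCF approach, the missing data are replaced by the last observed value of that variable".

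Data management {19} schedules the outcomes at baseline (week 1) and then at "time 2: immediately after the intervention, including post-treatment assessment (week 10), and time 3: 1-month follow-up (week 14"). The Adherence paragraph already plans to record modules completed and sessions attended.

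**The concern.** Sessions begin only after allocation, so the missed-sessions item cannot work as a screening criterion. It excludes randomised participants for poor attendance, while the analysis section says attendance does not matter. The COVID-19 sentence adds a second exit after randomisation, in nurses recruited because they care for COVID-19 patients.

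The other-therapy item is unclear. It may ask at screening about concurrent therapy, or it may exclude people later. The Interventions paragraph treats the same event as something to report.

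Attendance can depend on the allocated treatment. If these rules take people out of assessment, the plan itself creates missing primary outcomes. In a non-inferiority trial, anything that pulls the arms together makes a false claim of non-inferiority more likely. ISI values not collected at week 10 or week 14 cannot be recovered at the analysis stage.

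**Working it through.** **1. The rules side by side**

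| Event | Rule in {10} or {11a} | Possible before randomisation? | Analysis rule in {20a} |
|---|---|---|---|
| Three sessions missed in a row | Exclusion | No | Retained |
| Positive COVID-19 test | Does not continue the trial (garbled wording) | The rule addresses participants during the study | Retained |
| Other psychological therapy | Exclusion in {10}; report it in {11a} | Either reading | Retained |
| Pregnancy or breastfeeding | Exclusion | Yes | No conflict on that reading |

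The first row is a direct contradiction. The second adds to it. The third is an ambiguity.

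**2. What data an early leaver has.** The ISI is taken at weeks 1, 10 and 14 only. Someone who leaves trial and assessment during the eight weekly sessions has one value, the baseline, which is at least 15 by eligibility. There are then two possible treatments of that person.

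**3. If leavers are dropped.** The Sample size section gives 64 required and 80 after a 25% dropout allowance.

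- The 80 is reproduced as 64 × 1.25 = 80.
- Losing 25% of 80 leaves 80 × 0.75 = 60, below 64. Dividing instead gives 64 / 0.75 = 85.3, or 86.
- No SD is stated. With "one-tailed test, 5% significance level, and 80% power", a margin of 4, no true difference and 32 per arm, the implied SD is 4 × √(32/2) / (1.645 + 0.842) = 6.4.
- At that SD, power with 30 per arm is Φ(4 / (6.435 × √(2/30)) − 1.645) = 0.78, against 0.80 with 32.

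The power loss is small. The larger cost is that the comparison becomes one of completers.

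**4. If baseline is carried forward, with equal exits.** Let f be the share leaving in each arm. Baseline means are equal in expectation under randomisation, so leavers contribute no difference and the expected difference is 4 × (1 − f) when the true difference is 4. With 40 per arm, SE = SD × √(2/40), and

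P(declare non-inferiority) = Φ((4 − 4(1 − f)) / SE − 1.645).

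Assumed inputs are f and SD. The SD is taken as unchanged by the carrying forward.

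| f | Expected difference | SD 5 | SD 6.4 | SD 8 |
|---|---|---|---|---|
| 0 | 4.0 | 5% | 5% | 5% |
| 0.10 | 3.6 | 9.9% | 8.6% | 7.8% |
| 0.25 | 3.0 | 22.6% | 17.1% | 13.9% |

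For f = 0.25 and SD 5: SE = 1.118, 1.0 / 1.118 = 0.894, and Φ(0.894 − 1.645) = 0.226.

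**5. If baseline is carried forward, with unequal exits.** Assume true ISI improvements of 8 points on iCBT-I and 4 on iMBSR, so the true difference is 4. The expected difference is 8 × (1 − f_CBT) − 4 × (1 − f_MBSR).

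- 35% leave iCBT-I and 15% leave iMBSR: 5.2 − 3.4 = 1.8.
- 15% leave iCBT-I and 35% leave iMBSR: 6.8 − 2.6 = 4.2.

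The first pattern strongly favours a non-inferiority claim. The second is slightly conservative.

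**The case against.** The strongest reply is that {20a} already settles the matter: everyone randomised is analysed, and LOCF fills the gaps. Every participant has a baseline ISI, so an all-randomised estimate can be computed. This stands as far as it goes. A reader might infer that the intended estimate cannot be derived at all, and the documents do not support that. What LOCF does not do is supply the missing outcome; section 4 of the working shows the cost.

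Second, no sentence says the surveys stop after an exit. The article condenses a fuller protocol, and its flow diagram and schedule figures are not visible here. So a reader may infer, but cannot state as fact, that the week 10 and week 14 values are lost. The COVID-19 sentence stands under the Interventions heading and could mean being excused from sessions only.

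Third, a reader might say that most of the exclusion criteria are post-randomisation events. Only the missed-sessions item is so without doubt, since the other-therapy item has a plausible screening reading.

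Fourth, it is tempting to say that these exits must favour a false non-inferiority claim by leaving a comparison of completers. That mechanism applies only if leavers are dropped, and its direction depends on which arm loses more poor responders. The Background section attaches short-term worsening and discomfort to CBT-I, so removing poor responders there would flatter the comparator and make non-inferiority harder to show. Under LOCF, heavier exits from iCBT-I work the other way.

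Finally, a reader might suppose that COVID-19 exits alone would use up the 25% allowance. The documents give no infection rate, so this cannot be sized.

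None of these replies removes the contradiction over missed sessions. It does not arise from condensing, because both rules are stated and they disagree.

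**Conclusion.** The point holds as a conflict between stated rules. Eligibility {10} excludes on attendance after allocation, the Interventions paragraph adds a COVID-19 exit, and {20a} analyses everyone randomised whatever their attendance. The other-therapy item is ambiguous rather than contradictory.

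The consequence is conditional on the rules being applied as exits from assessment. On that reading, the equal-exit case is the clearest: with 25% leaving each arm, the false non-inferiority rate at the margin rises from 5% to roughly 14–23%, and with 10% leaving to roughly 8–10%. These figures rest on assumed SDs of 5 to 8, assumed exit shares and 40 per arm. With unequal exits no direction can be claimed in advance.

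**What to change.** Reconcile Eligibility {10}, the Interventions paragraph in {11a}, Concomitant care {11d} and Statistical methods {20a} by distinguishing three things: eligibility at baseline, stopping the sessions, and leaving assessment. Specifically:

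- State that missed sessions do not remove a randomised participant from follow-up or analysis. Attendance is already captured as adherence.
- State whether the other-therapy item applies at screening, later, or both, and make {10}, {11a} and {11d} agree.
- Say whether the COVID-19 sentence refers to the sessions or to the whole trial.
- State that everyone randomised is sent the existing week 10 and week 14 online surveys and is analysed in the allocated arm, unless consent is withdrawn.

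Whether sessions continue after infection or other therapy remains for the investigators to decide.

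The cost is protocol wording and sending existing survey links to people who have stopped sessions. Some of those responses will still be missing, so a missing-data method is still needed, but for fewer participants.

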#### Who will take informed consent? {26a}

Participants will be recruited through online announcements, flyers, and referrals (see Fig. 2). Potentially eligible individuals can apply to participate in the RCT via email or telephone contact. Interested participants will be informed of the study’s objectives, advantages, hazards, session numbers, confidentiality, and assurances of anonymity via email or telephone. Participants will be informed that they will be free to withdraw their consent or decline to participate. Upon agreement to participate, a survey invitation letter will be sent via email. Once the participants clicked on the survey link, an informed consent page will be opened. The nurses should be obtained an electronically signed informed consent form to proceed with the instrument section. Individuals who initially obtain a high score on the Insomnia Severity Index (ISI ≥ 15) will undergo an interview to ensure that the eligibility criteria are fulfilled. Two clinical psychologists evaluated the participants' personal history, mental status, personal resources, and suicide risk through 45 min of online clinical interviews.

**Fig. 2 Fig2:**
[figure not shown]
Graphical model of obtaining informed consent form process

#### Additional consent provisions for collection and use of participant data and biological specimens {26b}

Nurse will be requested if they agree to be contacted in the secondary analysis in future research participation. No biological specimens were collected as part of this trial.

### Intervention description {11a}

#### Interventions

The study (e.g., all assessments and treatments) will be administered online. All participants s will be requested not to change their lifestyle during the study and continue their daily routines, exercise, diet, and medications, and, if received any psychological treatment, inform the researchers. Each participants who receive positive COVID-19 test will be exempted to continue the trial. Before each session, participants will be requested to feel free in case of unpleasant experiences, potentially related to the trial. In case of emergency, the participant will receive further evaluation to make decision about continue or discontinue.

#### IMBSR group

The iMBSR intervention will be delivered in eight 2.5-h weekly sessions [74, 75], plus one 6-h weekend intensive silent retreat. The program is intended to facilitate increased awareness of one’s typical internal and external reactions to stress and introduce meditation techniques to promote healthy responses to stress. The core components of the IMBSR program comprise: (*a*) motivational interview; (*b*) physiological and psychological response to go; and (*c*) engage in a combination of the three major formal mindfulness practices (mindful hatha yoga sitting meditation and the body scan); (*d*) information on the effect of stress on health and options for mindful versus reactive responses to stress including non-judging, acceptance, patience, non-striving, and letting; and (*e*) course overview and relapse prevention. The program will be started with a module on motivation and readiness for change and treatment engagement and will be finished with a module for relapse prevention (for a more thorough explanation, see the supplemental data: appendix 2: part two).

#### ICBT-I group

The CBT-I group format is typically delivered over six to eight sessions [76–78]. The CBT-I is a multi-component intervention that will be administered and structured based on eight 2-h weekly sessions. The core components of the ICBT-I program comprise the following: (*a*) motivational interview, (*b*) sleep hygiene education; (*c*) sleep restriction; (*d*) stimulus control, (e) cognitive therapy, and (*f*) course overview and relapse prevention (for a more thorough explanation, see the supplemental data: appendix 2: part one).

#### Strategies to improve adherence to interventions {11c}

The motivational interview will be delivered to maximize the participants’ readiness for change and increase motivation to engage in treatment. Written feedback will also be provided to all nurses about the results of the health screenings. Reminder and follow-up messages will be sent to participants within three days before and after the each time-points

#### Relevant concomitant care permitted or prohibited during the trial {11d}

All standard care and stable medication are permitted other than concomitant administration of any other experimental treatment (see exclusion criteria).

#### Provisions for post-trial care {30}

No special provisions are offered.

## Outcomes {12}

The survey comprised the Dysfunctional Beliefs and Attitudes about Sleep Scale (DBAS) [79]), Brief Patient Health Questionnaire-9 (PHQ-9 [80]), Insomnia Severity Index (ISI [81]), The Five Facet Mindfulness Questionnaire (FFMQ [82]), and Client Satisfaction Questionnaire Adapted to Internet-Based Interventions (CSQ-I [83]).

### Primary outcome

The ISI is a brief scale employed to measure sleep problems and the severity of insomnia. This scale is sensitive to treatment response, which yields 86.1% sensitivity and 87.7% specificity [84]. Respondents will endorse seven items on a five-point scale ranging from zero = no problem to four = very severe, with higher scores indicating worse insomnia. ISI score ≥ 15 will be found to represent the moderately to severe clinical insomnia.

### Secondary outcome

#### Dysfunctional beliefs

DBAS is employed to measure erroneous beliefs, impaired cognition, expectations, and dysfunctional attitudes regarding poor sleep. Respondents will endorse ten items on Likert scales ranging from 0 (strongly disagree) to 10 (strongly agree).

#### Mindfulness

The FFMQ is a self-administered questionnaire employed to measure the five aspects of mindfulness. The questionnaire comprises five facets, including observation, description, aware action, nonjudgmental inner experience, and non-reactivity. The scale consists of 15 items (a three-item for each factor) that are rated on a five Likert scale from 1 (never) to (very often).

#### Adherence

Adherence can be conceptualized as the extent to which individuals experience or engage with the content of an online intervention. Adherence is measured by checking the number of modules completed in ICBT-I and group sessions attended in IMBSR. The feasibility of the both online interventions will be computed by the completion rate of each session and the proportion of participants completing the study.

### Participant timeline {13}

Study schedule of enrolment, intervention, and assessments is presented in Fig. 3.

**Fig. 3 Fig3:**
[figure not shown]
Study schedule of enrolment, intervention, and assessments

### Sample size {14}

The sample size is calculated according to the minimal difference recommendation for non-inferiority design [85]. The minimal important difference in the severity of insomnia is a decrease of eight scores on the ISI [84]. The non-inferiority margin is half the difference (4 points on ISI). Therefore, the treatment groups will be considered equivalent if their average ISI total scores do not differ by more than 4 points. Therefore, the study will detect the minimum clinically significant difference at a one-tailed test, 5% significance level, and 80% power. Finally, 64 participants will be required. Anticipation of 25% dropout rate, the required sample size was 80. To reach the desired sample size, the link for the study will be distributed and posted on online medical staff forums. Also, the trial information will be emailed to psychologist and psychiatrist to share the trial with their clients.

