### Randomization and masking {16a}

Participants will be randomly allocated to either of both conditions, using the permuted block technique. An independent statistician will generate the allocation schedule without any influence of the principal investigators or therapists. Random sequence block sizes (i.e., 2, 4, and 6) will be generated using a computer random number generator with equal allocation ratio (1:1). The statistician informs the observer staff and participants of the random allocation results via email. Randomization will be computerized with a concealed randomization. Block size will be unknown to the investigators and clinicians. The randomized intervention allocation is concealed until the statistical analyses of the resulting data will be completed and outcomes will be drawn. The psychological evaluators, statisticians, and assessors who measure and record the data will be blinded to the conditions and the participants’ groups. The research team will not be able to influence the randomization sequence and will have no access to allocations. The participants will be blinded to the study hypotheses.

The data safety and monitoring committee may request unblinded data throughout the trial period, but the initial data analyses should be blinded to protect against bias in decision. The investigator must report all code breaks (with reason) as they occur on the corresponding case report form page. Unblinding should not necessarily be a reason for study discontinuation.

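### The dropout allowance is miscalculated: 80 randomised retains the required 64 only up to 20% dropout, and 25% dropout leaves 60

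*Protocol article*

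**What the plan says.** All the planning figures are in the protocol article, Sample size {14}. The margin is set there: "The non-inferiority margin is half the difference (4 points on ISI"). The error rates follow as "a one-tailed test, 5% significance level, and 80% power". The evaluable number is given as "Finally, 64 participants will be required", and the number to enrol as "Anticipation of 25% dropout rate, the required sample size was 80".

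Two other sections bear on the point. Randomization and masking {16a} specifies an "equal allocation ratio (1:1"), so 64 is 32 per arm and 80 is 40 per arm. Statistical methods {20a} defines the analysis set: "Main analyses will be conducted on the intent-to-treat (ITT) approach, including all randomly allocated participants, regardless of attendance". The same section names last observation carried forward (LOCF) for missing values and a linear mixed model with a one-sided confidence limit for the non-inferiority test.

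Neither a standard deviation for the ISI nor an assumed true difference between arms is stated.

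**The concern.** The section gives three linked numbers: 64 needed, 25% lost, 80 enrolled. They cannot all hold. If a quarter of 80 participants are lost, 60 remain. The allowance was made by adding 25% of the evaluable number instead of working back from the number randomised.

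At stake is whether the plan meets its own requirement under its own dropout assumption. As written it does not: it falls 4 participants short of the number that it says is needed for the stated power. In a non-inferiority trial, lower precision widens the confidence interval and makes it harder to show that the upper limit lies below the 4-point margin.

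**Working it through.** **Inputs from the protocol.** Evaluable total 64, dropout 25%, number to enrol 80, margin 4 ISI points, one-sided alpha 5%, power 80% (all Sample size {14}); allocation 1:1 (Randomization and masking {16a}).

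**Assumptions, not in the protocol.** True difference zero; 64 is the total that just reaches 80% power; normal approximation; a dropout is a participant without an observed post-treatment ISI.

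**Step 1. Reproduce the plan's figure.**
- Adding the dropout rate: 64 × (1 + 0.25) = 80. This matches the stated 80 exactly.
- Dividing by the retained fraction: 64 / (1 − 0.25) = 85.3, rounded up to 86 (43 per arm). This does not match.

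**Step 2. What 80 delivers.**
- Retained at 25% dropout: 80 × 0.75 = 60 (30 per arm), 4 fewer than 64.
- Largest dropout that keeps 64: 1 − 64/80 = 20%.
- Check on 86: 86 × 0.75 = 64.5, which meets 64.

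**Step 3. Standard deviation implied by 64.** For n per arm,

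SD = margin / [(z for alpha + z for power) × √(2/n)], with 1.645 + 0.842 = 2.486 (unrounded sum).

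- n = 32: SD = 4 / (2.486 × 0.25) = 6.43. A t-based calculation gives 6.36.
- n = 31: SD = 4 / (2.486 × 0.254) = 6.33. Below this value a total of 62 would have been enough.

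So, if 64 is the smallest even total that reaches 80% power, the SD lies between about 6.33 and 6.43.

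**Step 4. Power with 60 (30 per arm).**

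Power = Φ[ margin / (SD × √(2/30)) − 1.645 ]

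| SD | margin / standard error | Power with 60 |
|---|---|---|
| 6.33 | 2.446 | 78.8% |
| 6.43 | 2.408 | 77.7% |

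The t-based calculation at SD 6.36 also gives 77.7%. The loss against 80% is therefore 1.2 to 2.3 percentage points.

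**Step 5. Dependence on the SD.** Sixty participants still give 80% power if the SD is at most 4 / (2.486 × √(2/30)) = 6.23. With 60, power is about 83% at SD 6, 72% at SD 7 and 61% at SD 8. At SD 7 or 8 most of that shortfall comes from the SD: even 64 would give only 74% and 64%.

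**The case against.** The strongest reply is that the primary analysis is by intention to treat with all randomised participants and that LOCF is named for missing values, so all 80 remain in the analysis set. Part of this stands. It would be wrong to say that only 60 will be analysed; the accurate statement is that 60 would have an observed post-treatment ISI. The section does not define dropout either, and someone who stops attending sessions may still complete the questionnaire. But the reply does not rescue the figure. For anyone lost before the post-treatment assessment, LOCF carries the baseline value forward and adds no post-treatment information. If imputed values counted in full, no dropout allowance would have been needed.

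A second reply is that the power loss cannot be established without a standard deviation. This also stands in part. A reader might infer that the trial definitely misses 80% power. The documents do not support that, because at an SD of 6.23 or less 60 would still suffice. What can be said is that, at the SD implied by the plan's own 64, power with 60 is below 80%.

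Three further inferences are tempting and should not be drawn.

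- **That the absent standard deviation is itself an error.** This is a journal article that refers to a cited recommendation for its method, and such detail is commonly left to the full protocol. Its absence makes 64 uncheckable here; it does not make 64 wrong.
- **That 64 was meant per arm, so the trial is half its intended size.** Sixty-four per group is the familiar answer for a 0.5 SD effect at two-sided 5% and 80% power. But the section states a one-tailed test and a 4-point margin, and has no per-arm wording. If 64 were per arm, the 80 derived from it would be per arm too.
- **That the section claims power to detect an 8-point difference.** Eight points is what it calls the minimal important difference, whereas Statistical methods {20a} attaches the term clinically significant difference to the 4-point margin. The phrase in the sample size section can be read as 4.

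**Conclusion.** The point holds as an arithmetic error in a stated planning figure. The figures 64, 25% and 80 are inconsistent: 80 allows for 20% dropout, 25% dropout leaves 60 with observed outcomes, and retaining 64 at 25% dropout would take 86. This conclusion needs no assumption beyond reading the dropout rate as a proportion of those randomised.

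The effect is small: 6 too few randomised, 4 too few retained, and power of about 78 to 79% in place of 80%. The power figure rests on 64 being the total that just reaches 80%, on a true difference of zero, and on the back-solved SD of about 6.33 to 6.43. The figures should be corrected, but the error does not threaten the design.

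**What to change.** Restate the dropout sentence in Sample size {14} in one of two ways, without enrolling more:

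1. 80 randomised allows for 20% dropout and retains 64; or
2. with 25% dropout, 80 randomised leaves about 60 with an observed post-treatment ISI, and power is about 78% under the standard deviation used in the calculation.

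The second version should take its power from the standard deviation actually used, in place of the value back-solved here. The statement should refer to participants with observed outcomes, so that it does not conflict with the intention-to-treat set of all 80.

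The cost is one restated sentence and a slightly less favourable dropout allowance or power. Design, enrolment and analysis are unchanged.
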